**Abstract**

# **Research protocol: PEGASUS: Paediatric European Group A Streptococcal United Study.**

**Version 1.4. 09-07-2024.**

## *Introduction*

Since 2022 there are reports of a rapid increase in invasive group A streptococcal infections (iGAS) in children in some but not all European countries. Detailed information on this increase is lacking. Furthermore, an increase in other invasive infections as well as the emergence of novel pathogens and disease entities is seen, such as MIS-C and severe hepatitis of unknown origin.

## *Aims*

To set up a European research network and describe the incidence, risk factors, clinical phenotypes, microbiology and resistance, treatment, and outcomes of iGAS in children across Europe. The network will subsequently be utilized for early alerting regarding the rise of other invasive and emerging infections in children. It will enable swift data collection pertaining to patient characteristics, presentation, progression, and treatment.

## *Methods*

International, retrospective cohort and observational surveillance study of children 0-18y attending the ED or admitted to the hospital with iGAS. Clinical and microbiological data, national vaccination schedules, and COVID non-pharmaceutical interventions (NPIs) will be collected and compared between countries. Subsequently, the network will be employed to raise alarms regarding the surge of other invasive infections or emerging infections in children. Anonymous data about these novel infections will be collected, similar to the data from iGAS (clinical characteristics and microbiological data). The study is a non-profit study.

## *Significance*

Our study will describe variation in the clinical phenotypes of iGAS, will aid in the understanding of its association with COVID NPIs and allow for comparison between countries. Furthermore, it will aid in early recognition of invasive and emergent infectious diseases in children and the reduction of outbreaks.

## **Introduction**

Since the COVID-19 pandemic and the implementation of non-pharmaceutical interventions (NPIs) to reduce the spread of SARS-CoV-2, a secondary effect has also been reported on the epidemiology of other viruses and bacterial infections. [Kruizinga 2021; Cohen trends 2022] At first, a decrease was seen in paediatric infectious diseases, followed by an off-season rebound with increased frequency of several common paediatric infectious diseases, such as bronchiolitis and gastroenteritis. [Cohen trends 2022]

In line with this, in 2022 several European countries as well as the United States, reported a rapid increase in children presenting with invasive group A streptococcal infections (iGAS). [van Kempen 2022; WHO; UK surveillance; Ladhani 2022] Many of those children had severe disease needing paediatric intensive care unit (PICU) admission or causing mortality. Furthermore, it was noted that many of these children had a preceding infection with influenza virus or varicella zoster virus (VZV). (1)

One hypothesis explaining the increase in iGAS is related to the various NPIs introduced between 2020 and early 2022, with the aim of containing the COVID-19 epidemic, and consequently resulting in an 'immunity gap' in children. (2)

Although this increase was seen in several European countries [WHO; van Kempen 2022; UK Surveillance; Ladhani 2022] this has not been reported in all European countries. Possible explanations for differences between countries include differences in COVID NPIs, differences in vaccination schedules for VZV and influenza, differences in circulating M protein genes (*emm* types) or underreporting due to the lack of a systematic surveillance system.

Importantly, detailed and systematic data collection on the clinical phenotypes is lacking, which is essential to better understand the current incidence, risk factors and outcome across European. However, given the rapid increase of iGAS cases, the increased case fatality rate described in a recent study in the Netherlands [van Kempen 2022] and the fact that it is a treatable disease when recognized early, prompt collection and dissemination of data are imperative.

The study will provide in-depth data on the clinical phenotypes, their management and their outcomes, to support clinicians dealing with children with iGAS in their clinical decision making. Increased awareness and early recognition can be lifesaving for children with iGAS and real-time surveillance will help to reduce outbreaks. Furthermore, it will provide public health policy makers with information regarding future NPIs and optimal vaccination schedules regarding other viral infections that may precede iGAS.

iGAS disease is just one example of how the landscape of PID has changed in recent years, and it is currently in a state of ongoing evolution. Other examples include the emergence of novel pathogens and disease entities such as MIS-C and severe hepatitis of unknown origin.

**Research protocol: PEGASUS: Paediatric European Group A Streptococcal United Study.**

***Version 1.4. 09-07-2024.***

We believe that our study will facilitate communication and data collection between countries and will facilitate responding promptly to international emergencies relating to rare childhood conditions where international studies can make a contribution to science or public health.

Furthermore, the European Centre for Disease Prevention and Control (ECDC) [ECDC] and the World Health Organization (WHO) [WHO] have recently urged for vigilance for a rise in iGAS cases.

Furthermore, our study will contribute to antimicrobial resistance data. Antimicrobial resistance is one of the top priorities of the European Union (EU).

Making use of existing and active research networks which will ensure commitment and success of the study.

## **Research questions**

### *Primary research questions*

1. What is the incidence of iGAS in children before, during and after COVID NPIs in different European countries?
2. Is there a change in clinical phenotypes and outcome during these periods?
3. Are there differences in clinical phenotypes and outcome between European countries?

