**Research protocol: PEGASUS: Paediatric European Group A Streptococcal United Study.**

**Version 1.4. 09-07-2024.**

*Retrospective study:*

Participating centres will be asked to report all iGAS cases in the specified time period.

Anonymized data will be collected in an online database. Data will be combined into one dataset and then compared and analysed in combination and per country. Insights from the retrospective data collection phase will be used for the development and implementation of the surveillance part of the study.

*Surveillance study:*

An online database will be used that for all new iGAS cases. Data collection will take place retrospectively once a month. Reporting by the participating centres will take place once a month and reminders will be sent regularly.

The data will be published online on a monthly basis without information that can be traced back to individual patients. Online data will be displayed as numbers as well as visually.

*Setting survey:*

An online survey will be sent to the lead investigators of each participating centre to collect information on national and regional aspects of healthcare possibly impacting iGAS incidence and the care for children with iGAS, such as vaccination schedules and vaccination rates and primary care availability.

*Surveillance study for other invasive or emergent infectious diseases*

An online database will be used for other invasive or emergent infectious diseases. Data collection will take place retrospectively once a month. Reporting by the participating centres will take place once a month and reminders will be sent regularly.

The data will be published online on a monthly basis without information that can be traced back to individual patients. Online data will be displayed as numbers as well as visually.

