**Inclusion criteria:**

- All children (1 month-18 years)
- attending the Emergency Department and/or admitted to the participating hospital - with iGAS infection or other invasive or emergent infectious disease.

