## **Data collection and online database**

The following variables will be collected: age, time of visit, gender, comorbidity, vaccination status, (viral) co-infection, e.g., VZV, influenza, respiratory syncytial virus (RSV), clinical symptoms, duration of symptoms before treatment, clinical diagnosis (e.g., pleural empyema, necrotising fasciitis, sepsis), culture/PCR/antigen detection results, *emm* type, antimicrobial resistance, treatment, hospital admission, ICU admission and death within 30 days.

During both the retrospective study as well as the surveillance study data will be collected anonymously in an online secure research database, hosted in the EU. Date of birth will be collected

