## **Research protocol: PEGASUS: Paediatric European Group A Streptococcal United Study.**

**Version 1.4. 09-07-2024.**

as rounded age and time of visit will be collected as shift (day, evening, night), month and year of presentation to ensure patient data cannot be traced back to individual patients. To ensure data will remain truly anonymous, settings will be instructed to not store a local key that can link database data to local patient data.

In case of existing surveillance (UK, Switzerland), existing data will be exported anonymously and combined into a database containing data from all participating countries. Harmonization of data will take place to ensure the comparability and completeness of the collected data.

A survey per hospital will collect information on national and regional aspects of healthcare, such as vaccination schedules, vaccination rates, availability of primary care, funding of health care system, availability of rapid testing for group A streptococcal disease, and COVID NPI's.

After data collection, data will be stored and analyzed on a local secure hospital server of Noordwest Ziekenhuisgroep.

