### **Statistical analysis**

First, descriptive analyses will be performed. Changes over time will be assessed by interrupted time-series analysis models. [Lenglart 2022]

Associations between NPIs and changes over time in iGAS incidence will be assessed by seasonally adjusted multivariable quasi-Poisson regression modelling and will be displayed as incidence rate ratios (IRR). [Lenglart 2022]

We will apply regression analyses to identify risk factors for adverse outcome. Statistical programs (SPSS and R) will be used for statistical analysis.

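### Primary question 1 asks for iGAS incidence by country, but the protocol names no population at risk, and its surveillance part cannot tell a month without cases from a month not reported

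*Protocol*

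**What the plan says.** Under *Primary research questions*, the Protocol asks "What is the incidence of iGAS in children before, during and after COVID NPIs in different European countries". *Plan of investigation* names incidence as a target of both the retrospective and the surveillance part, and the Methods paragraph of the Abstract says that the collected data will be compared between countries.

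The numerator comes from case reports. For the retrospective study, "Participating centres will be asked to report all iGAS cases in the specified time period". The *Inclusion criteria* restrict entry to children "attending the Emergency Department and/or admitted to the participating hospital". In *Data collection and online database* the list of variables opens with "The following variables will be collected: age, time of visit, gender, comorbidity, vaccination status, (viral) co-infection" and closes with "antimicrobial resistance, treatment, hospital admission, ICU admission and death within 30 days". Every item in it describes a child who is already a case.

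Centre-level information comes from a survey: "A survey per hospital will collect information on national and regional aspects of healthcare, such as vaccination schedules, vaccination rates, availability of primary care". The list goes on to funding, rapid testing and COVID NPIs. Two countries enter by another route: "In case of existing surveillance (UK, Switzerland), existing data will be exported anonymously and combined into a database containing data from all participating countries". The next sentence promises harmonisation so that the data are comparable and complete.

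In the surveillance part, centres report monthly and receive reminders. *Statistical analysis* plans interrupted time series and a seasonally adjusted quasi-Poisson regression for the association between NPIs and incidence, whose results "will be displayed as incidence rate ratios (IRR").

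**The concern.** Incidence is cases divided by person-time at risk. The Protocol describes the cases in detail but names nothing for the divisor: no catchment population, no child-years, no national child population. Nor does it name a record of which months each centre actually searched or reported.

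Three things are at stake. First, an absolute rate for any country is out of reach. Second, a difference in case numbers between countries mixes disease frequency with the size and number of participating hospitals. Hospital case series and surveillance exports may cover very different populations, so pooling them adds to this. Secondary question 7, which seeks to explain differences between countries, inherits the problem as far as those differences concern incidence. Third, the surveillance counts published online each month could fall because centres stop reporting.

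A statistical analysis plan can choose an offset, but it cannot supply centre-level data that no form collects. What is collected is fixed in this document.

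**Working it through.** The Protocol states no expected incidence, sample size or rate, so there is no figure of its own to reproduce. The check has two parts.

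**1. Search for a denominator and a reporting log**

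| Place in the Protocol | What it supplies | Population at risk? | Record of months covered? |
|---|---|---|---|
| Retrospective study | all cases in the window | no | only the nominal window |
| Surveillance study | monthly reports, reminders | no | no zero-case return |
| Case variables | attributes of cases | no | no |
| Setting survey / survey per hospital | care setting, vaccination, NPIs (open list) | none named | none named |
| UK and Swiss exports | existing surveillance cases | none named | none named |
| Statistical analysis | quasi-Poisson IRRs | no offset named | no |

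**2. What the counts can and cannot give**

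For a centre in period *p*, let λ be the true monthly rate, N the child catchment and c the fraction of cases captured. The expected monthly count is λ × N × c.

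- *Within a centre, between periods:* count ratio = (λ₁/λ₀) × (N₁/N₀) × (c₁/c₀). If N and c are stable, the last two factors are 1 and the count ratio is a valid IRR. If completeness dropped by an assumed 20%, the ratio would be multiplied by 0.80.
- *Between centres or countries A and B:* count ratio = (λ_A/λ_B) × (N_A/N_B) × (c_A/c_B). Here N_A/N_B has no reason to be 1. With equal true rates and equal capture, a catchment five times as large gives a count ratio of 5.

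*Absolute rate.* The window for the primary questions, taken as January 2018 to April 2023, is (2023 − 2018) × 12 + (4 − 1) + 1 = 64 months, or 64/12 = 5.33 years. With an assumed 40 cases, rate = 40 / (N × 5.33):

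| Assumed N | Rate per 100,000 child-years |
|---|---|
| 50,000 | 15.0 |
| 100,000 | 7.5 |
| 200,000 | 3.75 |
| 500,000 | 1.5 |

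The same count is compatible with a tenfold range.

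*Ranking.* With assumed figures for one common period, 30 cases among 300,000 children is 10 per 100,000, and 60 cases among 1,000,000 is 6 per 100,000. The larger count belongs to the lower rate.

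*Unreported surveillance months.* April 2023 to July 2024, the month of this protocol version, is (2024 − 2023) × 12 + (7 − 4) + 1 = 16 months. If k months are unreported and read as zero, apparent/true = (16 − k)/16. That is 0.875 for k = 2, 0.75 for k = 4 and 0.50 for k = 8. This assumes that missed months have average incidence and are never filled in later.

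**The case against.** The best defence is that the planned analyses are contrasts over time. In a series with a stable catchment the denominator cancels, and the resulting before/during/after ratios can be set side by side across countries. The primary question that explicitly asks about differences between countries is the third, on phenotypes and outcome. This stands, and it narrows the point. A reader might infer that no incidence comparison between countries is possible, or that the promised IRRs are meaningless. The documents do not support either inference: only absolute incidence and differences in level are lost. But question 1 asks for incidence in each country, and the Abstract promises comparison between countries, so the loss is real.

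The survey items are introduced as examples, and the instrument itself is not shown. It may ask for more than is printed, and outside population figures could serve the exports if that surveillance is national. This stands as a caveat. The Protocol plans neither, and a national figure does not give the catchment of selected hospitals.

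The promised harmonisation bears on comparability and completeness of what is collected. It cannot create a denominator or a reporting log.

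A reader might also extend the silent-month problem to the whole study. The retrospective part asks for all cases in a window that, for the primary questions, nominally starts in 2018 everywhere, so an empty month there is nominally a true zero. The ambiguity belongs mainly to surveillance, where reminders and retrospective entry soften it without removing it.

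Finally, a reader might fear distortion from using emergency attendances as the denominator. The Protocol proposes no such offset, so that is not a fault of this plan.

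**Conclusion.** The point holds in a limited form. Followed as written, the plan yields case counts. From these, absolute incidence and between-country differences in incidence level cannot be estimated. Within-centre period ratios can, and may be compared between countries, if catchment and reporting completeness are assumed stable. In surveillance from April 2023 onwards, absence of cases and absence of a report are indistinguishable; the retrospective part is less affected.

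The size depends on figures that the Protocol does not give. On the assumed inputs above, one count spans a tenfold range of rates, and unreported months scale the apparent surveillance rate to between 0.50 and 0.875 of the truth. The conclusion also assumes that the unseen survey instrument has no population or coverage item beyond those named. This should be fixed, but it does not invalidate the study, because the time contrasts survive under a stated assumption.

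**What to change.** - Add to the per-hospital survey, for each calendar year from the first data year, the child catchment population in the included age range. For the UK and Swiss exports, record the child population that the surveillance covers.
- Record for each centre the dates that its case search or reporting covered.
- In surveillance, require a monthly no-cases confirmation from now on. It cannot be applied to months already past, so obtain a one-time coverage statement for those.
- State in *Statistical analysis* that log(child population) is the offset for incidence levels and between-country comparison, and that only covered centre-months enter the models.
- Where no catchment is defensible, report within-centre period ratios only, state the stability assumption, and leave that centre out of between-country incidence.

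The cost is a few survey fields, one tick-box per centre per month and a wording change. The *Timetable* placed setting data collection in 2023 Q2 and this version is dated July 2024, so a supplementary survey round may be needed. The figures are centre-level, so the rule against a local patient key is untouched. The drawback is that catchments are approximate where hospitals overlap or take referrals, and the resulting rates should be presented with that caution.

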### *Secondary research questions*

4. Is there a change in *emm* types and other virulence factors during these periods?
5. Are there differences in antimicrobial resistance between periods and between countries?
6. Can we identify risk factors for iGAS infection (e.g., preceding infections, age)?
7. Can we explain differences between countries (e.g., differences in vaccination strategies, NPIs or *emm* types)?
8. Can we use this research network for early alarming on other invasive and emergent infectious diseases in children?

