### **Significance of the study**

Our study will describe changes in the clinical phenotypes of iGAS, will aid in the understanding of its association with COVID NPIs and allow for comparison between countries. It will identify risk factors for severe disease and will aid in early recognition of iGAS disease. Furthermore, it will aid in the early recognition of iGAS disease and the reduction of outbreaks. In addition to this, our study will contribute to antimicrobial resistance data. Antimicrobial resistance is one of the top priorities of the European Union (EU).

The COVID-19 pandemic seems to have had a profound impact on the epidemiology of paediatric infectious diseases in different ways, leading to several notable changes. (11)

Besides the increase in iGAS disease, an increase in other invasive pathogens, including meningococcal disease, is seen in the paediatric population. (11) These changes in the epidemiology of paediatric infectious diseases highlight the dynamic nature of microbial populations and the need for ongoing surveillance and adaptation in clinical practices and public health strategies.

Furthermore, seasonal shifts have been observed, of which the most notable one is the occurrence of unusual high respiratory syncytial virus (RSV) infections during the summer, which is typically considered an off-season for RSV. This atypical pattern of RSV infections has posed challenges in disease management and public health response. (11)

Additionally, the emergence of new clinical entities, such as Multisystem Inflammatory Syndrome in Children (MIS-C) (12–14) and severe acute hepatitis of unknown aetiology (15–17) has been observed. These novel conditions have presented clinicians with unique diagnostic and therapeutic challenges, further emphasizing the need for enhanced surveillance, research and collaboration of different countries and specialists with different backgrounds.

After setting up the framework for the collection of data on iGAS, the PEGASUS research network and framework that is initiated for iGAS disease, will be used to collect and share real time surveillance data on different invasive, novel and emergent paediatric infectious diseases across Europe.

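### Secondary question 6 asks for risk factors for iGAS infection, but individual exposures are recorded only in infected children, so the effect of preceding infection on acquiring iGAS cannot be estimated

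*Protocol*

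**What the plan says.** Among the secondary research questions, question 6 asks: "Can we identify risk factors for iGAS infection (e.g., preceding infections, age". Risk factors also appear as a topic in the Aims of the abstract and in Parts 1 and 2 of the Plan of investigation, without saying whether they are for infection or for outcome.

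The data come from cases:

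- Retrospective part: "Participating centres will be asked to report all iGAS cases in the specified time period".
- Surveillance part: "An online database will be used that for all new iGAS cases".
- Inclusion criteria: children seen at a participating hospital "with iGAS infection or other invasive or emergent infectious disease".
- Data items, recorded for those children, include "age, time of visit, gender, comorbidity, vaccination status, (viral) co-infection, e.g., VZV, influenza, respiratory syncytial virus (RSV".

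The setting survey adds hospital, regional and national context such as vaccination schedules and rates, primary care and COVID NPIs. It lists no age-specific population counts and no frequency of varicella or influenza among children.

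Under Statistical analysis, the only risk-factor analysis is this: "We will apply regression analyses to identify risk factors for adverse outcome". The only model that has iGAS occurrence as outcome and names an exposure concerns NPIs: "Associations between NPIs and changes over time in iGAS incidence will be assessed by seasonally adjusted multivariable quasi-Poisson regression modelling". The Significance section is in line with the adverse-outcome regression: "It will identify risk factors for severe disease".

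**The concern.** A risk factor for infection is a contrast between exposed and unexposed children in how often they get iGAS. It needs exposure data on children without iGAS, or person-time by exposure. The protocol plans neither for preceding infection, the first of the two examples in question 6. A regression for adverse outcome conditions on already having iGAS and so estimates something else.

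The Introduction already reports that many affected children had preceding influenza or varicella, and it says that the study should inform vaccination policy for such infections. A bare case proportion given as the answer to question 6 would invite the inference that the preceding infection raises the risk of iGAS, and the data could not support it.

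**Working it through.** The protocol states no figure on this point, so there is nothing to reproduce. The check sets question, population, data and analysis side by side, and then asks whether the case data determine the quantity sought.

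**Step 1: what each part of question 6 needs, and what is planned**

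| Element | Preceding infection | Age |
|---|---|---|
| Exposure in cases | Collected (viral co-infection) | Collected |
| Exposure in children without iGAS | Not collected, no source named | Needs only population counts by age; none named |
| Stated analysis with iGAS occurrence as outcome | None (NPI model only) | None by age; overall incidence is primary question 1 |
| Stated risk-factor regression | Adverse outcome | Adverse outcome |

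**Step 2: do the case data fix the odds ratio?**

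Let p1 be the exposed share among cases and p0 the exposed share in the source population over the same time window. Then

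OR = [p1/(1 − p1)] / [p0/(1 − p0)].

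The study yields p1 only. Neither value is in the protocol. The figures below are assumptions for illustration, with p1 = 20%, so that p1/(1 − p1) = 0.20/0.80 = 0.25.

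| Assumed p0 | p0/(1 − p0) | OR |
|---|---|---|
| 2% | 0.0204 | 0.25/0.0204 = 12.25 |
| 5% | 0.0526 | 0.25/0.0526 = 4.75 |
| 10% | 0.1111 | 0.25/0.1111 = 2.25 |
| 20% | 0.2500 | 0.25/0.2500 = 1.00 |
| 30% | 0.4286 | 0.25/0.4286 = 0.58 |

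One and the same case series fits a strong risk factor, no association and an inverse association.

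**Step 3: does comparing periods help?**

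No. The Introduction itself says that viral infections fell and then rebounded around the NPIs. So p0 moves over time, and a change in p1 between periods cannot be read as a change in, or evidence of, an effect.

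**Step 4: could Part 4 supply the comparator?**

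Only in part. Its children are also infected, and the protocol does not name them as a comparison group. The Timetable sets up that registry in 2023 Q4, whereas the retrospective iGAS cohort runs from January 2015 to April 2023. Centres are asked to report all iGAS cases for that period, and there is no matching retrospective request for other invasive infections.

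**The case against.** Several points can be made for the protocol.

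- *Age can be answered.* This stands. Age is recorded, incidence is already primary question 1, and only population denominators by age are missing. A reader might infer that question 6 as a whole is unanswerable. The documents do not support that; the gap in design concerns preceding infection.
- *The adverse-outcome regression may never have been meant for question 6.* This also stands. The Statistical analysis section does not link the two, and the regression may simply serve the aim on severe disease. A reader might infer that the protocol has swapped one estimand for another, but the text does not show it. What it does show is that no stated analysis addresses preceding infection as a risk factor for iGAS.
- *A statistical analysis plan may give the model.* It may, but it cannot supply a comparator that is never collected. Repair afterwards is also hard, because centres are told to keep no local key to the anonymous records.
- *There is population-level information.* The survey collects vaccination schedules and rates, and the incidence model is multivariable. These are not frequencies of infection. An ecological analysis against external influenza or varicella series would be possible, but none is named and it would not give individual-level risk.
- *The vaccination-policy aim does not rest on question 6 alone.* This is correct. Question 7 compares vaccination strategies between countries, so that aim does not fall with question 6.

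**Conclusion.** The point holds in a limited form. As designed, the study cannot estimate the effect of preceding infection on acquiring iGAS, because exposure is recorded only in children with iGAS or another invasive or emergent infection and no population frequency is named. The illustration gives an odds ratio anywhere from 12.25 to 0.58 for the same 20% of cases exposed. Its inputs are all assumed, and it shows non-identifiability, not a likely size of effect. Age is not affected in the same way and needs only a named denominator.

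It might also be inferred that the data already planned provide a ready control group in Part 4. They do not for the 2015–2023 cohort.

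This should be fixed but is not critical: it is one of five secondary questions, and primary questions 1 to 3 do not depend on it.

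**What to change.** 1. Reword question 6 to ask for risk factors for adverse outcome (severe disease) among children with iGAS, consistent with the Statistical analysis and Significance sections. The protocol does not define adverse outcome there. ICU admission and death within 30 days are among the collected variables, but choosing them as the outcome is a decision for the investigators.
2. Align the mentions of risk factors in the Aims and in Parts 1 and 2 of the Plan of investigation.
3. Report preceding infections as descriptive characteristics of cases, with a statement that they do not estimate the risk of acquiring iGAS.
4. Report age as age-specific incidence, and name the population denominator.
5. Optionally, compare iGAS with other invasive infections, limited to the centres and calendar period in which Part 4 also collects cases. Label it a case-case comparison that does not estimate population risk.

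Items 1 to 3 cost protocol wording only. Item 4 needs a source of population counts. Item 5 needs no new data within the overlapping period, but extending it to the 2015–2023 cohort would need new data collection. If the infection question is kept for preceding infection, a comparator group or a named source of population exposure must be added with a matching analysis. The downside of the rewording is a narrower claim.
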